**Methods/Design:**

A single-centred blinded randomized controlled trial will be conducted in Brisbane, Australia. Participants (n = 252) will include those ≥ 18 years, mechanically ventilated for ≥ 48 hours and diagnosed with a sepsis syndrome. Participants will be randomised to an intervention arm which will undergo an early targeted rehabilitation program according to the level of arousal, strength and cardiovascular stability and a control group which will receive normal care.

The primary outcome measures will be physical function tests on discharge from ICU (The Acute Care Index of Function and The Physical Function ICU Test). Health-related quality of life will be measured using the Short Form-36 and the psychological component will be tested using The Hospital Anxiety and Depression Scale. Secondary measures will include inflammatory biomarkers; Interleukin-6, Interleukin-10 and Tumour Necrosis Factor-α, peripheral blood mitochondrial DNA content and lactate, fat free muscle mass, tissue oxygenation and microcirculatory flow.

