### Primary Outcome Measures

All primary outcomes will be measured at baseline (recruitment) and at ICU discharge and quality of life at 6 months post hospital discharge. The primary outcome measures will report the level of physical functioning and quality of life (long-term effects) of the participants. Physical function will be measured using the Acute Care Index of Function (ACIF) and the Physical Function ICU Test (PFIT).

The ACIF will essentially rate simple physical function (transfer bed to chair, sit to stand independently) of the patient on leaving the ICU [62]. The PFIT is a newly developed clinical tool for testing functional strength and endurance capacity in ICU patients. It consists of a battery of tests assessing endurance, muscle strength, cardiovascular capacity and functional ability which are domain representative of physical function and specific for the use of higher functional assessment in the critically ill [63]. These have been chosen as corresponding measuring instruments as they have demonstrated reliability, validity and responsiveness in the ICU population [63,64].

Quality of life will be measured using the Short Form-36 (SF-36) Health Survey Questionnaire. Information from the next of kin will be used to provide proxy scores which have been demonstrated to have good reliability and validity [65].

The constructs of psychological well being will be measured using the anxiety subscale of the Hospital Anxiety and Depression Scale (HADS) as psychological wellbeing is known to be highly correlated to functional physical outcomes [66].

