### Sample size

Clinically important difference and the standard deviation estimates used in our sample size calculations were based on a previous clinical trial [64]. Sample size was calculated using the ACIF [62] for hypothesis testing with a type I error rate of 0.05 and 0.025 with Bonferroni adjustment and type II error rate of 0.20 (80% power). A minimum of 35 per group (70 total) is required to detect a minimum clinical difference (effect size) of 0.7 for physical functional outcomes which will yield clinically significant results for the main hypothesis achievable by intervention. Projection of the sample size after adjusting for attrition or withdrawal rates, participation refusals and possible death due to sepsis; based on admission and mortality rates in the RBWH ICU, 126 patients per group (252 in total) will be required.

A smaller number of patients will undergo mtDNA, tissue oxygenation and microcirculatory measurements as these will be tested as pilot investigations. To test these secondary hypotheses, a minimum of 58 per group is required to detect a minimum clinical difference of 0.8 for clinically significant changes in mitochondrial DNA [78], a minimum 91 per group is required to detect a clinical difference of 0.4 and 59 per group is required to detect a minimum clinical difference of 0.7 for clinically significant changes in tissue oxygenation [45] and microcirculation [46] respectively, all corrected for with Bonferroni adjustment of 0.025.

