### Data Management and Statistical Analysis

A baseline comparison using both student t-tests and chi-square for equal proportions of demographic data will be done between groups at enrolment. Data will be analyzed using SPSS Version 17.0. The distribution, range of scores and heterogeneity will be examined for participants in both groups. Mean changes scores, standard deviations and 95% confidence intervals will be calculated and specific analysis detailed under each outcome measure will be performed. Repeated measures, between/within analysis of variance (ANOVA) will be performed to investigate for the main effects of time and group. Post hoc analyses will then be performed to ascertain where the differences occur. A Bonferroni correction will be used as the post hoc measure as there are multiple outcome measures. Analysis will be by both intention-to-treat and per-protocol method. Any violations of the protocol will be noted. Statistical significance will be set at p < 0.05 and p < 0.025(two-tailed). All efforts will be taken to avoid missing data but if it occurs a carry forward imputation will be done and linear mixed modelling will be used for overall analysis. Reasons for loss of follow up will be recorded.

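### Two significance thresholds are stated without saying which outcome each governs, and 0.025 is a split for two tests while up to four instruments stand as primary

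*Protocol article*

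**What the plan says.** **Thresholds.** The section Data Management and Statistical Analysis states: "Statistical significance will be set at p < 0.05 and p < 0.025(two-tailed". It does not say which outcome or test each value applies to. The Sample size section bases its calculation on ACIF and gives a "type I error rate of 0.05 and 0.025 with Bonferroni adjustment and type II error rate of 0.20 (80% power". The same section later uses 0.025 for the mitochondrial DNA, tissue oxygenation and microcirculation calculations, which are secondary.

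**Primary set.** The abstract says: "The primary outcome measures will be physical function tests on discharge from ICU (The Acute Care Index of Function and The Physical Function ICU Test". Its next sentence, before the secondary measures begin, reads "Health-related quality of life will be measured using the Short Form-36 and the psychological component will be tested using The Hospital Anxiety and Depression Scale", with no label as primary or secondary. In the body, the section Primary Outcome Measures says: "The primary outcome measures will report the level of physical functioning and quality of life (long-term effects) of the participants". Four instruments are described under that heading: ACIF, PFIT, SF-36 and the HADS anxiety subscale. HADS is there by placement only, because the summary sentence names function and quality of life. The primary hypothesis under Hypotheses and Aims also names function and quality of life.

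**Multiplicity and populations.** The analysis section adds: "A Bonferroni correction will be used as the post hoc measure as there are multiple outcome measures". It gives no number of tests. It also says: "Analysis will be by both intention-to-treat and per-protocol method".

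**The concern.** A success rule should give one answer for any p-value. Here a primary result at p = 0.03 is significant under one stated threshold and not under the other, and nothing in the article decides between them.

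The second difficulty is that 0.025 controls the error over two tests, while the article supports counts of two, three (function by two instruments, plus SF-36) or four. If more than two outcomes can each support a claim at 0.025, or if 0.05 is used for any set of two or more, the chance of at least one false positive exceeds 5%. At stake is whether a claim of benefit carries the error rate the reader will assume.

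**Working it through.** **Inputs from the article.** Thresholds 0.05 and 0.025, two-tailed (analysis section). Standardised effect 0.7, power 80%, 35 per group (Sample size). Number of primary instruments: two labelled in the abstract, four listed in the body, three if HADS is not counted. Correlation between outcomes is not given; 0.3 to 0.7 is assumed below to show a range.

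**1. Which alpha produces 35 per group?** Normal approximation: n per group = 2(z₁₋α/₂ + z₀.₈)² / d², with d = 0.7 and z₀.₈ = 0.842.

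- α = 0.05: 2(1.960 + 0.842)² / 0.49 = 32.0, so 33 (t-test solution 33.02, so 34).
- α = 0.025: 2(2.241 + 0.842)² / 0.49 = 38.8, so 39 (t-test 40.08, so 41).
- α = 0.0125: 2(2.498 + 0.842)² / 0.49 = 45.5, so 46 (t-test 47.1, so 48).

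The stated 35 agrees, to within two patients, with two-sided 0.05. It does not agree with two-sided 0.025.

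**2. Power at 35 per group.** Normal approximation: Φ(d√(n/2) − z₁₋α/₂), where d√(n/2) = 0.7 × √17.5 = 2.928.

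- α = 0.05: Φ(0.968) = 83% (t-test 82%).
- α = 0.025: Φ(0.687) = 75% (t-test 74%).
- α = 0.0125: Φ(0.431) = 67% (t-test 64%).

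**3. Family-wise error, independent tests.** 1 − (1 − α)^k:

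| Primaries k | each at 0.025 | each at 0.05 |
|---|---|---|
| 2 | 1 − 0.975² = 4.9% | 1 − 0.95² = 9.75% |
| 3 | 1 − 0.975³ = 7.3% | 1 − 0.95³ = 14.3% |
| 4 | 1 − 0.975⁴ = 9.6% | 1 − 0.95⁴ = 18.5% |

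**4. Allowing for correlation.** With four equally correlated normal test statistics and an assumed correlation of 0.3, 0.5 or 0.7, the error is 9.1%, 8.3% or 7.0% at 0.025, and 17.4%, 15.6% or 13.0% at 0.05. For two primaries at 0.025 it is 4.8% to 4.3% over the same range.

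**5. Reading the rows together.** Of the combinations in the table, only two primaries, both at 0.025, stay within 5%. The article does not commit to that combination, and its own figure of 35 per group was not sized for it.

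**The case against.** The strongest reply is that the intended rule can be guessed. The sample size section writes 0.025 with the words Bonferroni adjustment attached, so 0.05 may be the nominal level and 0.025 the adjusted one. The analysis section gives multiple outcome measures as its reason for the correction, so it would be wrong to infer that the plan ignores multiplicity across outcomes. This stands as evidence of intent. It does not settle the rule: the correction is described as a post hoc measure following the ANOVA, no number of tests is given, and 0.05 stays in the threshold sentence. Nor does 0.025 identify the two tests. It could be ACIF and PFIT, or the two domains of function and quality of life, and it is also used for three secondary measures.

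A reader might also infer more than the article supports in these respects:

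- *That the abstract contradicts the body.* It does not call SF-36 or HADS secondary; it leaves them unlabelled. The hypothesis, the Primary Outcome Measures section and the Key Messages all pair function with quality of life. The difference is one of labelling.
- *That each SF-36 score is a separate primary test, with a much larger error.* The article does not say which SF-36 scores are tested or that they are tested separately, so no such figure is used here.
- *That the two analysis populations are a serious fault.* Planning both is ordinary, and the deciding one is often named in an analysis plan, which is not shown.
- *That a choice after seeing the data is planned.* The wording leaves room for it; nothing states it.

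The independent-test figures are also near the upper end of the range. ACIF and PFIT both measure function, and the article itself describes psychological wellbeing as strongly related to functional outcome, so the correlated figures are the more realistic ones.

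**Conclusion.** The point holds as a fault in a stated decision rule. For a primary result with 0.025 < p < 0.05 the article gives two answers, and its 0.025 threshold controls the error at 5% for two primaries but not for the three or four that the body supports. The size is 7.3% for three and 9.6% for four at 0.025 under independence, and about 7% to 9% for four with assumed correlations of 0.3 to 0.7. If 0.05 is the operative threshold, it is 9.75% for two and 18.5% for four under independence (about 13% to 17% for four with the same correlations).

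One might conclude that the trial as a whole is underpowered at 0.025. That does not follow. The 74% to 75% applies to 35 evaluable patients per group. Enrolment of 126 per group yields 35 only if 1 − 35/126 = 72% are lost. No attrition rate is stated, so whether enough evaluable patients would remain cannot be checked.

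**What to change.** State one primary set in identical terms in the abstract, the primary hypothesis and the Primary Outcome Measures section. Give each primary test one two-sided alpha, with the alphas summing to 0.05, or use Holm. Two options fit:

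- ACIF and PFIT at ICU discharge at 0.025 each, with SF-36 and HADS anxiety secondary. This matches the abstract's labels but requires the primary hypothesis to be reworded.
- Quality of life kept primary, with alpha split over the actual number of primary tests, for example 0.0125 each for four. This matches the stated hypothesis and the body.

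In either case, delete the unassigned p < 0.05 for the primary family and say that the Bonferroni adjustment applies across the primary outcomes, with the number of tests. As a minor addition, name intention-to-treat as the deciding analysis and per-protocol as supportive.

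The cost is wording plus a restated sample size figure. Using the article's effect size of 0.7 and 80% power, the evaluable number per group becomes 39 to 41 at 0.025, or 46 to 48 at 0.0125. With 126 enrolled per group, reaching 41 allows a loss of up to 1 − 41/126 = 67%, and reaching 48 up to 1 − 48/126 = 62%. The assumed attrition rate should be stated so that this can be judged. The changes should be made before any outcome data are seen by group.

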### Sepsis Syndrome

Sepsis is a systemic inflammatory response associated with an infectious insult. It is the leading cause of death in critically ill patients and is often associated multi organ failure [8]. The inflammatory cytokines associated with sepsis such as Interleukin-6 (IL-6), Interleukin-10 (IL-10) and Interleukin-1β (IL-1β) are found to be correlated with the severity of the disease, the evolution of organ failure as measured by the SOFA score and mortality [9]. Physiological responses to inflammation as described in Table 1 in addition to the presence of a suspected or proven infection has been an internationally accepted definition for "Sepsis" [8,10]. Increasing sepsis severity correlates with increasing mortality, rising from 25-30% for severe sepsis to 40-70% for septic shock [11].

**Table 1 T1:** Criteria for SIRS and Sepsis syndromes (modified from Dellinger et al [57])

Syndrome	Criteria	Mortality
Systemic inflammatory response syndrome (SIRS) any two or more of the following criteria	▪ HR>90 bpm ▪ RR>20/min or PaCO_2_< 32 mmHg ▪ WCC< 4 × 10^9 ^cells/L or > 12 × 10^9^ cells/L or > 10% immature bands 12,000 ▪ T>38°C or <36°C	

Sepsis	▪ SIRS + proven infection	15%

Severe sepsis	▪ Sepsis + failure of one or more organs	20%

Septic shock	▪ Severe sepsis + cardiovascular failure despite adequate fluid resuscitation (usually SABP <90 mmHg or >40 mmHg from baseline)	45%

HR; Heart rate, RR; Respiratory Rate; WCC; White Cell Count; T; Temperature, SIRS; Systemic Inflammatory Response Syndrome, SABP; Systolic Arterial Blood Pressure.

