### Demographics

Patient demographic information will be collected at baseline (recruitment) and ICU and hospital discharge and will include; age, gender, primary reason for readmission to ICU, Acute Physiological and Chronic Health Evaluation II (APACHE II)[58], Sequential Organ Failure Assessment (SOFA) score [59], Charlson Comorbidity Index [60], time on mechanical ventilation, length of ICU and hospital stay, readmissions to ICU and 90-day mortality.

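### Carry-forward imputation makes no exception for death, so recruitment scores can become primary results, and its relation to the named mixed model is not stated

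*Protocol article*

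**What the plan says.** The rule is in the Protocol article, Data Management and Statistical Analysis: for missing data, "if it occurs a carry forward imputation will be done and linear mixed modelling will be used for overall analysis". The section also plans a repeated-measures ANOVA. It does not say whether the mixed model replaces the imputation, follows it, or stands beside an ANOVA on imputed data. On populations it says "Analysis will be by both intention-to-treat and per-protocol method". It also commits to recording why patients were lost.

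Under Primary Outcome Measures the article sets the schedule: "All primary outcomes will be measured at baseline (recruitment) and at ICU discharge and quality of life at 6 months post hospital discharge". Physical function (ACIF and PFIT) therefore has two time points. Quality of life (SF-36) has a third, and next of kin may supply proxy scores.

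Death appears in three other places:
- **Sample size** counts it among the losses: "Projection of the sample size after adjusting for attrition or withdrawal rates, participation refusals and possible death due to sepsis", leading to "126 patients per group (252 in total) will be required".
- **Sepsis Syndrome** gives background mortality, "rising from 25-30% for severe sepsis to 40-70% for septic shock". Table 1 there gives 15% for sepsis, 20% for severe sepsis and 45% for septic shock.
- **Demographics** lists "readmissions to ICU and 90-day mortality" among the descriptive data.

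The article has no separate rule for patients who die before an assessment.

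**The concern.** Carry-forward needs an earlier value to copy. For ACIF and PFIT the only one is the recruitment value, taken in a patient ventilated for at least 48 hours. Read with intention-to-treat, the rule gives an ICU death a discharge result equal to baseline. Someone who died is then analysed as someone who did not change. The same happens to a patient who leaves ICU without being assessed. For quality of life, a patient who dies or is lost before 6 months keeps an ICU-discharge or baseline SF-36 score.

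Three things are at stake:
- The physical-function effect is diluted, because imputed patients contribute no treatment effect and add spread.
- A difference in mortality between arms can by itself produce a difference in function or quality of life.
- Copied values are analysed as if observed, so standard errors do not reflect how little was measured.

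The mixed model does not cure this if it is fitted to the filled-in data. Fitted to the observed data, it would not need the imputation.

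**Working it through.** **1. The plan's own figure.** Inputs from Sample size: effect size 0.7 (taken as a standardised difference) and 80% power; two-sided testing is from the analysis section. At alpha 0.05, n per group = 2(1.960 + 0.842)² / 0.7² = 32.04, so 33; the t-test solution is 33.02, so 34. The stated 35 reproduces to within 2 patients. At alpha 0.025 the results are 39 and 41, a separate matter that does not affect this point. The step from 35 to 126 cannot be reproduced because no loss rate is given.

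**2. Dilution under carry-forward.** Assumptions, none given by the article for this trial: survivors' change from baseline has SD 1; control survivors gain g SD and treated survivors g + 0.7; a proportion m in each arm dies before ICU discharge and is assigned change 0. Then:

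- difference = 0.7(1 − m)
- variance in an arm with survivor mean μ = (1 − m) + m(1 − m)μ²
- standardised effect d = difference / √(average of the two variances)

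Example, m = 0.30 and g = 2: difference 0.49; variances 0.70 + 0.21 × 4 = 1.540 and 0.70 + 0.21 × 7.29 = 2.231; average 1.885; SD 1.373; d = 0.357.

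Mortality of 15% to 45% is an assumed range, taken from Table 1. The last two columns give n per group for 80% power at two-sided 0.05.

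| m | carried, of 126 per arm | difference | d, g = 1 | d, g = 2 | n, g = 1 | n, g = 2 |
|---|---|---|---|---|---|---|
| 0.15 | 19 | 0.60 | 0.57 | 0.47 | 49 | 70 |
| 0.20 | 25 | 0.56 | 0.53 | 0.43 | 56 | 86 |
| 0.30 | 38 | 0.49 | 0.47 | 0.36 | 73 | 124 |
| 0.45 | 57 | 0.39 | 0.38 | 0.28 | 110 | 207 |

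At m = 0.30 and g = 3, d = 0.28.

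**3. Power, if 126 per arm are randomised and all are kept by imputation.** At d = 0.357, power is about 81% at alpha 0.05 and 72% at 0.025. At d = 0.276 (45% mortality, g = 2) it is about 59% and 48%. With survivors only, 126 × 0.70 ≈ 88 or 126 × 0.55 ≈ 69 per arm at d = 0.70, power exceeds 98% at alpha 0.05.

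**4. A difference from mortality alone.** Suppose there is no treatment effect in survivors, whose mean lies Δ SD above the carried value. Treated minus control = (1 − m_T)Δ − (1 − m_C)Δ = (m_C − m_T)Δ. With 20% mortality in control and 30% in the treated arm this is −0.10 SD for Δ = 1 and −0.20 SD for Δ = 2. With the mortalities swapped, the signs swap. If survivors score below the carried value (Δ negative), which is possible for SF-36, the sign also reverses and the arm with more deaths looks better. At Δ = −1 the same mortalities give +0.10 SD.

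**The case against.** The strongest reply is that the article never says deaths are imputed. It speaks of missing data that it hopes to avoid, and Sample size covers death by enrolling more patients, which fits a reading in which deaths drop out. The carry-forward might also serve only the ANOVA, with the mixed model fitted to observed data. Both readings are possible, so it would be too strong to say that the imputation defeats the mixed model. But the rule has no exception for death and intention-to-treat retains those patients. The ambiguity is itself a defect in a stated rule, not a detail left to an analysis plan. Carry-forward is also a poor rule for living patients who miss the discharge test.

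A second reply is that no death-handling method is neutral. If baseline is near the floor, carry-forward resembles a worst score, and a worst-rank analysis also combines function with survival. A survivor analysis conditions on a post-randomisation event. This stands, and it is why worst rank is proposed only as a sensitivity analysis.

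Third, the size depends on undocumented gains. At a 2 SD gain and 30% mortality, power at 0.05 would still be about 81% with 126 per arm. That is correct; the estimate is nevertheless diluted.

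A reader might infer four stronger points, which the article does not support:
- **That a death at 6 months cannot be told from loss to follow-up, because mortality is listed only to 90 days.** Reasons for loss are to be recorded, and death is an obvious one.
- **That about 72% of final values would be copies of baseline (1 − 35/126 = 72.2%).** That allowance includes refusals, who have no trial baseline to carry.
- **That most missing values will be deaths.** The mortality figures are background, without a time horizon. Eligibility excludes moribund patients and shock unresponsive to maximal treatment, and no other attrition rate is given for comparison.
- **That the quality-of-life bias must favour the arm with more deaths.** Its direction depends on whether survivors score above or below the carried value.

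**Conclusion.** The concern holds. As written, the rule can turn a recruitment score into the primary physical-function result for anyone without a discharge score, deaths included, and an earlier SF-36 score into the 6-month result. Its relation to the mixed model is undefined.

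Under the stated assumptions (deaths fixed at baseline, equal mortality, survivor SD 1), a true effect of 0.70 SD shrinks to between 0.28 and 0.47 at 30% mortality, and to about 0.28 at 45% with a 2 SD gain. Unequal mortality alone can create 0.10 to 0.20 SD. Mortality and gains are illustrative and are not trial figures. What follows from the text is the mechanism: a copied baseline where no outcome exists.

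**What to change.** - Delete the carry-forward rule.
- Make the linear mixed model already named the primary analysis, fitted to observed data without imputation.
- State that no function or quality-of-life score is imputed after death and that the estimate refers to survivors. For this to be true, the model at each assessment must be limited to patients alive at that time. If the recruitment records of patients who died stay in, the model implicitly extrapolates discharge scores for them.
- Report deaths by arm beside each primary outcome.
- Add an intention-to-treat worst-rank analysis, with death before assessment ranked lowest, as a sensitivity analysis.

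The cost is a rewording of the analysis section and one extra analysis, with no additional patients. The downside is that survivors are a group defined after randomisation, so their comparison is not fully protected by it. The deaths by arm and the worst-rank analysis accompany it for that reason.
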